### Statistical analysis

In case data on outcomes are incomplete, the investigators will use multiple imputation to replace missing values, taking data clustering into account. No interim analyses are planned.

There are two co-primary outcomes: improvement in the MAI at 12 months, defined as decrease of at least one point, and improvement in the AOU at 12 months, defined as at least one less prescribing omission. Both outcomes will be tested separately; success is indicated by the significance of at least one of the two tests.

For the co-primary outcomes, the investigators will present and compare the proportion of patients whose MAI and AOU score improved in the control and intervention group. The relative difference between groups will be determined in a mixed-effects logistic model with a random intercept at the GP level to account for clustering. The effect measure for the primary outcomes will be odds ratios (OR). The relative difference will be presented as OR with a 95% CI. The primary analysis will be an intention-to-treat analysis. In a per-protocol analysis, the investigators will only evaluate patients who adhered to the protocol and exclude patients who violate any inclusion or exclusion criteria.

Secondary binary outcomes will be evaluated like the primary outcomes. Secondary continuous outcomes will be analysed using random-effects linear regression with a random intercept at the GP level. Models will also be adjusted for the baseline value as a covariate. Secondary count outcomes will be analysed using random-effects Poisson regression with a random intercept at the GP level.

Health economic analyses will assess (i) resource use and cost differences between the trial arms, (ii) differences in quality-adjusted lifetime between the trial arms, expressed as QALYs, and (iii) a comparison of cost-effectiveness between intervention and standard care.

Because cluster-randomisation may not balance characteristics between groups to match individual-level randomisation, the investigators will adjust each model for patient-level and physician-level variables to account for case-mix differences between groups and potential recruitment bias in a sensitivity analysis. They will also account for the correlated nature of data among GPs by using multilevel mixed-effects models. Unadjusted models will be provided for information only.

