### Sample size

Sample size calculation is based on testing the two co-primary outcomes for superiority and uses the Bonferroni-approach to account for multiple testing. Based on trial results published by Gallagher *et al* in 2011, the investigators assumed that 35% of patients in the control group and 60% of patients in the intervention group will improve their total MAI score (at least one less point) and that 10% of patients in the control group and 30% of patients in the intervention group will have a better AOU score (at least one fewer prescribing omission).^49^ Intracluster correlations (ICC) of 0.01–0.05 are typically found for binary outcomes in elderly individuals.^50^ The investigators conservatively assumed an ICC of 0.05 to calculate the sample size. The investigators fixed the type I error at a Bonferroni-corrected two-sided alpha level of 0.025.

Based on a two-sample comparison of proportions and a prespecified number of clusters of about 40 (about 20 per arm), seven patients per cluster are required to detect a difference of 25% between the two groups in the proportion of improvement in the MAI, with a power of 90%. The number of 40 GPs was selected arbitrarily for feasibility reasons. Using the same assumption for the AOU, the investigators found they also need seven patients per cluster to detect a difference of 20%. The investigators thus need a sample of 280 patients (140 per arm) to provide 81% power to detect a significant improvement in both the MAI score and the AOU. To account for attrition from dropout or death (15% estimated), the number of patients per cluster was increased to eight (max. ten), so the final sample size should be about 320 patients (160 per arm). The investigators will closely support GPs to help them reach the target sample size.

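### The co-primary odds ratios are to be shown with 95% CIs although each is tested at two-sided 0.025, so an interval can exclude 1 when the prespecified test has failed

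*Protocol article*

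**What the plan says.** The Sample size section of the protocol article concerns superiority tests of the two co-primary outcomes. It "uses the Bonferroni-approach to account for multiple testing" and states: "The investigators fixed the type I error at a Bonferroni-corrected two-sided alpha level of 0.025".

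The Statistical analysis section gives the success rule: "Both outcomes will be tested separately; success is indicated by the significance of at least one of the two tests". It names the odds ratio from a mixed-effects logistic model, with a random intercept for the GP, as the effect measure for the co-primary outcomes. On precision it says: "The relative difference will be presented as OR with a 95% CI".

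The 0.025 level appears only in the Sample size section. The article nowhere mentions a 97.5% interval, and nowhere says that the 95% interval is descriptive or unadjusted for the two tests.

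**The concern.** Two levels are attached to the same two comparisons. The tests run at 0.025 each, and because a win on either outcome is enough, that correction is needed. The intervals are set at 95%, the level that goes with an uncorrected 0.05 test.

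The two therefore disagree whenever a co-primary p-value lies from 0.025 to below 0.05: the prespecified test fails, yet the printed interval for the odds ratio excludes 1. Many readers judge a primary result from its interval, and 95% is the only inferential level named in the section that describes the analysis. A borderline result would then appear in the primary table in a form that conflicts with the trial's own conclusion.

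**Working it through.** **Inputs (protocol article, Sample size and Statistical analysis sections).** Two co-primary outcomes; two-sided 0.025 per test; success if at least one is significant; 95% CI for each odds ratio; ICC 0.05; about 20 clusters per arm; 90% power per outcome. Assumed rates: "35% of patients in the control group and 60% of patients in the intervention group will improve their total MAI score" and "10% of patients in the control group and 30% of patients in the intervention group will have a better AOU score".

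**1. Was the design sized at 0.025?** The number per arm without clustering is n = [z(1−α/2)·√(2p̄(1−p̄)) + z(power)·√(p₁(1−p₁)+p₂(1−p₂))]² / (p₂−p₁)². The cluster size for k = 20 clusters per arm is m = n(1−ICC)/(k − n·ICC).

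| Outcome | α | n per arm | m | Rounded up | Rounded up, with continuity correction |
|---|---|---|---|---|---|
| MAI | 0.025 | 97 | 97×0.95/(20−4.85) = 6.08 | 7 | 7 (6.76) |
| AOU | 0.025 | 98 | 98×0.95/(20−4.90) = 6.17 | 7 | 7 (6.94) |
| MAI | 0.05 | 82 | 82×0.95/(20−4.10) = 4.90 | 5 | 6 (5.52) |
| AOU | 0.05 | 82 | 4.90 | 5 | 6 (5.68) |

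The article's seven per cluster, and 7 × 40 = 280 patients, are reproduced at 0.025 and not at 0.05. So 0.025 is the working level of the design.

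**2. Which interval matches the test?** On the log-odds scale, with a normal approximation, a two-sided test at α rejects exactly when the (1−α) interval excludes 0. For α = 0.025 that is the 97.5% interval.
- Multiplier at 95%: 1.960. Multiplier at 97.5%: 2.241.
- Ratio: 2.2414/1.9600 = 1.144, so the matching interval is 14.4% wider on the log-odds scale.

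**3. How often can test and interval disagree?**
- Under the null, per outcome: 0.05 − 0.025 = 2.5%.
- Both nulls true, outcomes independent, both tests fail but at least one 95% interval excludes 1: 0.975² − 0.95² = 0.9506 − 0.9025 = 4.8%.
- The article gives no correlation between the outcomes. If the two p-values always coincided, this chance would be 2.5%; it cannot exceed 2 × 2.5% = 5%.
- Under the design alternatives (140 per arm, design effect 1 + 6×0.05 = 1.30): MAI 96.2% − 93.0% = 3.1% from unrounded values; AOU also 3.1%.

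**4. What would a rule based on the intervals cost?** Both nulls true, both directions counted:
- Success if either p<0.025: 1 − 0.975² = 4.94% under independence, bound 5%.
- Success if either 95% interval excludes 1: 1 − 0.95² = 9.75% under independence, bound 10%. It falls to 5% if the two tests always agree.

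**5. Illustration for the MAI.** Assume a 35% rate in both arms for the standard error, 140 per arm and design effect 1.30, so the effective number is 140/1.30 = 107.7 per arm. SE(log OR) = √(2/(107.7×0.35×0.65)) = 0.286. A result with p = 0.035 then gives:
- OR 1.83
- 95% CI 1.04 to 3.20, which excludes 1
- 97.5% CI 0.96 to 3.47, which includes 1

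With this standard error, test and 95% interval disagree for odds ratios from exp(1.960×0.286) = 1.75 to exp(2.241×0.286) = 1.90.

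**The case against.** The strongest reply is that success does not rest on the interval. The Statistical analysis section rests it on the significance of the tests, and the Sample size section, immediately before it, gives their level. Read together, the rule is complete: success if either p<0.025. Familywise error is then at most 5%, whatever interval is printed. The interval sentence concerns presentation, and nominal 95% intervals beside multiplicity-adjusted tests are common practice.

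This stands, and it limits the point. A reader might infer from the mismatch that the promised error control is lost, or that the trial runs at a familywise error of 9.75%. The article does not support that: 9.75% belongs to a rule it does not state. A reader might also count it a fault that 0.025 is not repeated in the Statistical analysis section. Stating it once is enough, and a condensed article may leave the repetition and the labelling of intervals to a fuller document.

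What the reply does not remove is the possible conflict in the published result. The article fixes the interval level for the very comparisons that it tests at 0.025, and gives no sign that the interval is unadjusted.

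**Conclusion.** The mismatch is real, but it is one of reporting and interpretation. With p<0.025 as the criterion the type I error is controlled at 5%. The chosen interval nevertheless contradicts the test whenever a co-primary p-value falls from 0.025 to below 0.05. Under two true nulls there is about a 4.8% chance that the trial fails on both tests while at least one interval excludes 1. That figure assumes independent outcomes and agreement of test and interval on the log-odds scale; without independence the upper bound is 5%. Under the design assumptions disagreement has a chance of about 3.1% per outcome. Only if success were read from the 95% intervals would familywise error rise, to about 9.75% under independence and 10% at most.

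Severity: minor to moderate. Sample size, power, model and decision rule are unaffected.

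**What to change.** In the Statistical analysis section, present the two co-primary odds ratios with 97.5% CIs and say that significance of a co-primary test means two-sided p<0.025. If 95% CIs are wanted for comparison with other trials, add them in a separate column labelled as unadjusted and not for the success decision. Secondary outcomes can keep 95% CIs.

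A lighter alternative would keep the 95% CIs, state that they are descriptive and rest success on p<0.025 alone. That removes the ambiguity but leaves an interval that can point the other way from the test.

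The cost is a sentence or two, settled before the unblinded results are seen, and primary intervals about 14% wider on the log-odds scale.

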### Assessment of primary outcome

The primary endpoint is medication appropriateness, measured jointly by the MAI and the AOU, in each study group. While the AOU assesses underprescribing, the MAI is a tool to assess different elements of medication prescribing (eg, overprescribing, drug–drug interactions, etc).^7 39 40^

Blinded study team members assess the MAI for each regular medication study participants take and assess the AOU for each chronic condition study participants have. The investigators will use the weighted 10-item version of the MAI developed by Samsa *et al.*
40 However, due to the rapidly changing drug prices the MAI item on cost-effectiveness will not be included. The criteria of the MAI, including corresponding weights, can be found in table 2. Using clinical data and the predefined operational definitions for each item, the assessor rates each medication on a three-point scale ranging from A=appropriate, B=marginally appropriate, C=inappropriate. Each ‘inappropriate’ rating will receive the respective weight from table 2, while the weight of ratings ‘appropriate’ and ‘marginally appropriate’ will be 0. Thus, the score for each medication ranges from 0 to 17 (as the cost-effectiveness criterion will not be included).^40^ A higher score indicates a greater degree of medication inappropriateness. The investigators will calculate the score for each medication and then calculate the summated score for each patient, by summing up the scores for each medication. For the AOU, assessors decide for each chronic condition if there is (i) no omission, (ii) marginal omission, or (iii) omission of indicated medication.^41–43^ For each patient, the investigators will calculate how many omissions there are.

**Table 2 T2:** Criteria of the Medication Appropriateness Index including weights

	Item	Weight
1	Is there an indication for the drug?	3
2	Is the medication effective for the condition?	3
3	Is the dosage correct?	2
4	Are the directions correct?	2
5	Are the directions practical?	1
6	Are there clinically significant drug–drug interactions?	2
7	Are there clinically significant drug–disease/condition interactions?	2
8	Is there unnecessary duplication with other drug(s)?	1
9	Is the duration of therapy acceptable?	1

Item 10 ‘Is this drug the least expensive alternative compared to others of equal utility?’ has been excluded.^40^

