Despite taking precautions to avoid and reduce selection bias (cluster randomisation to avoid learning effect, screening lists for patient recruitment, randomisation of GPs after patient recruitment), selection bias is still possible because of the study design. Since GPs can recruit patients outside of the screening list for practical reasons, not all patients are recruited randomly. Patients who are more engaged and/or more likely to adhere to advice may be more likely to be enrolled in the trial, which might decrease the representativeness of the study population and the generalisability of the results. The investigators will use data from FIRE to compare the characteristics of study participants with those of non-participants.The investigators chose a usual care sham intervention in the control group to improve patient blinding, but this design does not eliminate the risk GPs in the control group will be contaminated by the thematic of the trial (risk of deviating from their previous routine prescribing practices). In addition, this sham intervention might lead GPs to suggest medication changes that could improve the appropriateness of patients’ medications.Outcome assessment is based on self-reported data from patients and relatives and on data from FIRE, so some events may be missed. To ensure FIRE data is as complete as possible, GPs must code their patient’s medication intake and their diagnoses correctly. Diagnoses require ICPC-2 codes. GPs were instructed, in face-to-face meetings, about how to code and update data in their EMR for patients in this trial.^26^
Like all interventions that take an eHealth approach (STRIPA intervention in this case), people have different perceptions of what is user-friendly. New procedures may seem complicated in comparison to usual care. The investigators tried to simplify the process by (i) using EMR data so that GPs do not have to enter all the data themselves, but only update them if needed; and (ii) giving detailed instructions for using STRIPA in writing and in an online video training.Unrestricted randomisation designs, such as the block randomisation used in this trial, are more likely to result in imbalance of factors by chance.^51^

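### The co-primary models name no baseline score although a patient at zero cannot improve, and the protocol does not settle whether the adjusted or the unadjusted model decides success

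*Protocol article*

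**What the plan says.** All of the following is in the protocol article.

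- **Endpoints (Statistical analysis).** There are two co-primary outcomes. One is a 12-month MAI score that is lower than at baseline by one point or more. The other, for underprescribing, is "improvement in the AOU at 12 months, defined as at least one less prescribing omission". Significance on either one counts as success.
- **Co-primary model (same section).** The between-group comparison uses a "mixed-effects logistic model with a random intercept at the GP level to account for clustering". No fixed covariate is named.
- **Baseline adjustment (same section, next paragraph).** "Models will also be adjusted for the baseline value as a covariate" comes between the model for secondary continuous outcomes and the model for secondary counts.
- **Other adjustment (same section, last paragraph).** In a sensitivity analysis, "the investigators will adjust each model for patient-level and physician-level variables to account for case-mix differences between groups". The variables are not listed. The paragraph ends: "Unadjusted models will be provided for information only".
- **Floors (Assessment of primary outcome).** For the MAI, "the score for each medication ranges from 0 to 17", and these are summed over a patient's drugs. The AOU result is a count of omissions. Both have a minimum of zero, and both are to be scored at baseline, 6 and 12 months.
- **Randomisation (Randomisation; Discussion).** Allocation of about 40 GPs is unstratified. The limitations say that such designs "are more likely to result in imbalance of factors by chance".

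**The concern.** Each endpoint is a dichotomised fall in a bounded score. A patient who starts at zero is certain to be a non-improver whatever the treatment does. Above zero, a higher starting score leaves more room to fall. Baseline therefore fixes the outcome for part of the sample and probably predicts it in the rest. Leaving it out of the decisive test gives up precision for no saving, since the score is already planned for every participant.

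The protocol is also uneven here. Assessment of secondary outcomes lists the degree of overprescribing (by MAI) and of underprescribing (by AOU). If these are analysed as continuous outcomes, they are baseline-adjusted, while the primary tests built from the same scores are not.

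The second strand is which model counts. If adjustment belongs to a sensitivity analysis, the unadjusted model is primary. If unadjusted models are only informative, the adjusted model is primary. Both cannot hold, and with two tests, either of which can establish success, the choice should be fixed before the data are seen.

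**Working it through.** **Inputs from Sample size.** MAI improvement 35% v 60%; AOU improvement 10% v 30%; two-sided alpha 0.025 per outcome; power 90%; ICC 0.05; about 20 clusters per arm; 7 patients per cluster; 140 per arm.

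**Step 1: reproduce the plan's figure.** Patients per arm under individual randomisation:
n = [2.2414·√(2p̄(1−p̄)) + 1.2816·√(p₁(1−p₁)+p₂(1−p₂))]² / (p₂−p₁)².
- MAI: (2.2414·0.7062 + 1.2816·0.6837)² / 0.0625 = 96.8, so 97.
- AOU: (2.2414·0.5657 + 1.2816·0.5477)² / 0.04 = 97.01, so 98.

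Patients per cluster: m = n(1−0.05)/(20−0.05n). This gives 6.08 (MAI) and 6.17 (AOU), or 6.76 and 6.94 with continuity correction. All round up to 7. Joint power is 0.9 × 0.9 = 0.81. The protocol's 7 per cluster, 280 patients and 81% reproduce.

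**Step 2: power without the covariate.** The design effect is 1 + 6·0.05 = 1.3, so the effective n per arm is 140/1.3 = 107.7. Power is 93.0% for each outcome without continuity correction, and about 90% with it. There is no shortfall against plan.

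**Step 3: what the floor hides.** Let f be the share of patients at zero at baseline. The documents do not give f, so it is an assumption. The planned intervention rates cap it at 1 − 0.60 = 40% for the MAI and 1 − 0.30 = 70% for the AOU. Among patients above zero the rates become p/(1−f), and the effective n becomes 107.7(1−f).

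| Outcome | f | Rates above zero | Power, patients above zero | Gain over 93.0% (points) |
|---|---|---|---|---|
| MAI | 5% | 36.8% v 63.2% | 94.3% | 1.3 |
| MAI | 10% | 38.9% v 66.7% | 95.5% | 2.5 |
| MAI | 20% | 43.7% v 75.0% | 97.9% | 4.9 |
| MAI | 30% | 50.0% v 85.7% | 99.6% | 6.6 |
| AOU | 20% | 12.5% v 37.5% | 94.7% | 1.7 |
| AOU | 40% | 16.7% v 50.0% | 97.1% | 4.1 |
| AOU | 60% | 25.0% v 75.0% | 99.7% | 6.7 |

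**Step 4: the planned type of model.** A simulation of 40 clusters of 7 fitted a random-intercept logistic model with a likelihood-ratio test at 0.025, 600 runs per setting. Baseline omissions were drawn as Poisson, and the MAI entered as log(1 + score). These distributions, and the strength of the baseline effect, are assumptions.

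| Outcome | f | No covariate | With baseline score |
|---|---|---|---|
| AOU | 30% | 95.2% | 96.8% |
| AOU | 50% | 97.7% | 99.3% |
| MAI | 5% | 93.0% | 93.5% |
| MAI | 15% | 94.5% | 97.8% |
| MAI | 25% | 95.8% | 98.8% |

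Gains here are about 0.5 to 3.3 points, smaller than in step 3 because a single score term does not use the floor fully. With no treatment effect (AOU, f = 50%), rejection was 1.8% without and 2.7% with the covariate. The Monte Carlo standard error is √(0.025·0.975/600) = 0.6 points, so both agree with 2.5%.

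**Step 5: chance imbalance in f.** The SD of the between-arm difference is √(2f(1−f)·1.3/140), assuming that f clusters like the outcome. At f = 40% this is √(0.48·1.3/140) = 6.7 points. Multiplying by the mean improvement rate above zero gives the shift in the raw difference: 6.7 × 0.333 = 2.2 points. Over the ranges tried, a one-SD imbalance shifts the raw difference by 1.4 to 3.3 points for the AOU (f 20–60%) and 1.5 to 4.2 points for the MAI (f 5–30%), against planned differences of 20 and 25.

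**The case against.** **Details may be in the SAP.** The article names a model family and a random intercept; it does not say that nothing else enters, and covariate lists are often left to the SAP. That stands as a caution. It does not remove the point, because the article itself states where baseline adjustment applies and itself contains the two statements on adjustment that conflict.

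**Imbalance is addressed.** A reader might infer that chance imbalance goes uncorrected. The documents do not support that: the sensitivity analysis covers each model, and the closing sentence could even mean that adjusted models lead. What remains is that the baseline scores are not named there and that a sensitivity analysis does not decide success.

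**Imbalance is not bias.** A reader might also infer that an unlucky allocation invalidates the unadjusted test. It does not. Chance imbalance across randomised clusters is sampling error that the test and interval already cover, and simulated type I error is nominal.

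**The trial is not underpowered by this.** Correct, as step 2 shows. A much larger loss can be produced by assuming a smaller effect: one simulation at 10% v 20% on the AOU, using a cluster-level t-test and 40–60% at zero, moves from 47% to 53–63%. That effect is not the planned one, nor is that test the planned model, so it does not set the size here.

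**The MAI may hardly be affected.** Patients take at least five drugs, each rated on nine weighted items, so a total of zero may be rare. This stands: at 5% the simulated gain is 0.5 points, within simulation error.

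**Conclusion.** The point holds as a matter of efficiency and clarity. As stated, the co-primary models carry no baseline score, although the floor makes it a determinant of the outcome for some patients, and the text does not settle whether the adjusted or the unadjusted model is primary. Validity is not in question and planned power is met. Power forgone at the planned effects is roughly 1 to 7 percentage points by formula, and up to about 3 in the mixed-model simulation. Both rest on an assumed share at zero that the protocol does not give. That the adjustment is missing from the decisive analysis is the natural reading of the article, but not a certain one.

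**What to change.** 1. State which model decides each co-primary test, and reconcile the placing of adjustment in a sensitivity analysis with the demotion of unadjusted models.
2. In the primary analysis, add the baseline MAI sum score to the MAI model and the baseline number of omissions to the AOU model as fixed covariates, with their functional form fixed in advance. Use the score itself: an indicator for zero at baseline would predict non-improvement perfectly and its coefficient could not be estimated.
3. Report the share of patients at zero at baseline by arm, for each score.
4. Keep the model without covariates as supportive.

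The cost is wording only, settled before analysis; no new data are needed. The downside is that the odds ratio becomes conditional on baseline and is no longer directly comparable with one from the model without covariates. The raw proportions by arm, already planned, should therefore be shown beside it.
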